### Participant recruitment

#### Participant inclusion criteria

Participants must be adult (18 years or above) Syrians under temporary protection who are Arabic-speaking and residing in Turkey. The inclusion criteria include the following: (1) scoring greater than 16 on the WHO Disability Assessment Schedule 2.0 (WHODAS 2.0) for health and disability and (2) scoring greater than 15 on the Kessler-10 Psychological Distress Scale for psychological distress [25, 26].

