#### Sample size and power calculations

The Vrije University (VU) University Medical Centre Department of Epidemiology and Biostatistics carried out the power calculations for this study. Considering previous studies with PM+ in Peshawar, Pakistan, and Nairobi, Kenya, we aim for a conservatively estimated small to medium Cohen’s d effect size of 0.4 in the PM+ group at the 3-month follow-up [13, 15]. Power calculations suggest a minimum sample size of 133 participants per group (power = 0.90, a = 0.05, two-sided). Considering an expected 30% attrition at the 3-month follow-up, we aim to include a total number of 380 participants (190 in the Group PM+/E-CAU group and 190 in the E-CAU group).

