### Group PM+

PM+ is a brief, trans-diagnostic psychological intervention based on cognitive behavioural therapy techniques and developed by the WHO [12, 27]. It consists of five sessions delivered in five consecutive weeks and aims to reduce symptoms of depression, anxiety, PTSD and related conditions. Groups are separated by gender, and gender-matched facilitators will lead groups consisting of six to eight participants (T1). Sessions include evidence-based strategies of stress management, problem-solving, behavioural activation and strengthening social support. PM+ is designed to be delivered by non-specialist helpers who receive an 8-day training in PM+. These Arabic-speaking non-specialist helpers, who are called facilitators, are supervised by psychologists and psychiatrists who have participated in the PM+ training-of-trainers program. Supervision consists of weekly, face-to-face group supervision and individual supervision when needed.

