#### Primary outcome measure

The primary outcome measure of this study is the Hopkins Symptom Checklist (HSCL-25). This assesses anxiety and depression symptom levels at 3-month follow-up assessment [31]. It has 25 items, namely two sub-scales for depression (13 items) and anxiety symptoms (10 items) and two items related to somatic symptoms. These items are scored on a 4-point Likert scale.

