#### Secondary outcome measures

The secondary outcome measures are (1) the PTSD Checklist for DSM-5 (PCL-5) to assess the severity of post-traumatic stress reactions, (2) Psychological Outcomes Profiles (PSYCHLOPS) to assess self-identified problems, (3) the Client Service Receipt Inventory (CSRI) to assess health service utilization and productivity impacts, and (4) WHODAS, which is also part of the screening and which assesses functional disability [32, 33]. In addition, perceived access to health services will be measured (see Fig. 2). The PCL-5 has 20 items scored on a 0–4 scale, adding up to a total severity score of 80, and higher scores indicate higher levels of symptomatology. PSYCHLOPS consists of four questions on three domains: problems (two questions), function (one question) and wellbeing (one question). Problem and function questions are asked in the form of free texts, and the responses are scored on an ordinal 6-point scale, producing a maximum score of 20. The CSRI includes questions about resource use for health and social care services, informal care, and productivity as a result of functionality in people with mental disorders. The CSRI has been adapted for Syrians in Turkey to match Turkish health-care services that are available to Syrians. Relevant unit costs will be attached to service utilisation to estimate changes in use of health services and health-care costs, while Turkish minimum wage rates will be used to conservatively estimate changes in costs associated with both informal family care and lost productivity by the patient from work.

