## Statistical methods

Descriptive analyses will be carried out in Statistical Package for the Social Sciences (SPSS) and Hierarchical Linear Modelling (HLM) analyses in Stata version 11.2. Across all analyses, two-tailed tests will be reported with a *P* value of less than 0.05. To estimate the effectiveness and cost-effectiveness of Group PM+, the following data analysis methods will be conducted. First, to examine whether there are differences between conditions, *t* tests (continuous variables) or chi-squared test (categorical variables) will be conducted at baseline to compare the two intervention arms (i.e., Group PM+/E-TAU vs. E-TUA) for normally distributed data; Mann–Whitney tests will be conducted for continuous non-normally distributed data.

Intention-to-treat (ITT) analyses, including all randomly assigned participants (*N* = 380) and treatment completers’ (per protocol) analyses, will be conducted. The primary outcomes of the trial will be the ITT analyses. A linear mixed model will be used for the primary endpoint analysis to estimate the intervention effect, which will have intervention as fixed effects, baseline measurement of primary endpoint as covariate, and participants as random effects.

The mean difference between the two treatment arms at each visit/time together with its 95% confidence interval will be derived from the mixed model. A covariate-adjusted mixed model for the primary endpoint will be performed by adding pre-specified covariates at baseline (gender, age, education, traumatic experiences, post-migration difficulties, etc.) into the above model. Missing data will be treated as missing at random. No imputations of missing values will be made, as multilevel models can deal with missing data [40]. Qualitative data from the process evaluation will be analysed thematically in accordance with the framework approach [41]. Interview transcripts will be coded by using Nvivo version 11 [42].

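### Adding screening K10, screening WHODAS and gender to the primary model is a small, nearly free improvement; the planned model, adjusted for baseline HSCL-25 alone, is valid

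*Protocol article*

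**What the plan says.** The primary outcome is the HSCL-25: "This assesses anxiety and depression symptom levels at 3-month follow-up assessment" (Primary outcome measure). Statistical methods specifies a linear mixed model for it with intervention as a fixed effect, "baseline measurement of primary endpoint as covariate, and participants as random effects". A second, covariate-adjusted model adds "pre-specified covariates at baseline (gender, age, education, traumatic experiences, post-migration difficulties, etc.) into the above model". Neither list names K10 or WHODAS, and gender is only in the second.

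Both scales are eligibility scores. Participant inclusion criteria requires "scoring greater than 16 on the WHO Disability Assessment Schedule 2.0" and "scoring greater than 15 on the Kessler-10 Psychological Distress Scale for psychological distress". Secondary outcome measures lists "WHODAS, which is also part of the screening and which assesses functional disability". Gender shapes delivery of the intervention: "Groups are separated by gender, and gender-matched facilitators will lead groups consisting of six to eight participants" (Group PM+).

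The sample size section assumes a "conservatively estimated small to medium Cohen’s d effect size of 0.4 in the PM+ group at the 3-month follow-up", 133 participants per group for 90% power at two-sided 0.05, and 30% attrition at that visit, giving 190 per arm. Statistical methods treats missing data as missing at random and makes no imputations.

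**The concern.** An eligible participant cannot be randomised without a K10 and a WHODAS score, so both are complete by design and measured before allocation. The protocol uses K10 as its screening measure of psychological distress, which is also the construct that the abstract assigns to the HSCL-25. WHODAS adds functional impairment. If either predicts 3-month HSCL-25 beyond baseline HSCL-25, conditioning on it shortens the primary confidence interval without new data.

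The second issue is missing data. With no imputation step, a baseline variable can support the missing-at-random assumption only by being in the model. If more impaired participants attend follow-up less often, for example, a model that includes WHODAS makes that assumption easier to defend than one that leaves it out. At stake is some precision and some robustness of the primary estimate, not its validity.

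**Working it through.** **1. The plan's own figure.** Inputs from Sample size and power calculations: d = 0.4, power 0.90, two-sided α = 0.05. By the normal approximation, n = 2(1.960 + 1.282)²/0.4² = 131.3, so 132 per arm. The two-sample t-test gives 132.3, rounded up to 133. Then 133/0.70 = 190 per arm, 380 in total. The stated figures reproduce, and no covariate enters them. Power at 133 per arm on this basis is 90.4% (90.1% by t-test).

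**2. Power of the planned model.** Let r be the correlation between baseline and 3-month HSCL-25 (not given; assumed). The residual SD, in units of the outcome SD, is s = √(1 − r²), and power = Φ(d/(s√(2/133)) − 1.960), with √(2/133) = 0.1226.

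- r = 0.4: 94.5%
- r = 0.5: s = 0.866, d/SE = 3.767, power 96.5%
- r = 0.6: 98.3%

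On this point the planned model already exceeds its design power.

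**3. Adding covariates.** Let p be the joint partial R² of the added covariates beyond baseline HSCL-25 (assumed). Then s = √((1 − r²)(1 − p)), the SE is multiplied by √(1 − p), and the gain is worth 266/(1 − p) − 266 analysed participants. With r = 0.5:

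| p | SE reduction | Equivalent extra participants (on 266) | Power, d = 0.4 | Power, d = 0.3 |
|---|---|---|---|---|
| 0 | 0% | 0 | 96.5% | 80.6% |
| 0.01 | 0.5% | 3 | 96.6% | 81.0% |
| 0.03 | 1.5% | 8 | 96.9% | 81.8% |
| 0.05 | 2.5% | 14 | 97.2% | 82.6% |
| 0.10 | 5.1% | 30 | 97.8% | 84.6% |

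**4. What p might be.** For K10 alone, let r₁ be baseline HSCL-25 with follow-up, r₂ K10 with follow-up, and r₁₂ the two baseline scales with each other. Then R² = (r₁² + r₂² − 2r₁r₂r₁₂)/(1 − r₁₂²), and p = (R² − r₁²)/(1 − r₁²). Take assumed ranges r₁ 0.4–0.6, r₂ 0.35–0.50, r₁₂ 0.6–0.7:

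- (0.5, 0.35, 0.70): R² = 0.1275/0.51 = 0.25 = r₁², so p = 0.
- (0.4, 0.50, 0.60): R² = 0.17/0.64 = 0.2656, so p = 0.1056/0.84 = 12.6%.
- Midpoint (0.5, 0.425, 0.65): R² = 0.1544/0.5775 = 0.2673, so p = 0.0173/0.75 = 2.3%.

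In illustrative sets with K10 and WHODAS together, the joint p is 0 to 0.01 when baseline K10 and HSCL-25 correlate at 0.7. It reaches 0.06 to 0.10 only when they correlate at 0.4–0.5 while K10 still predicts follow-up at 0.4. No separate contribution of gender was calculated.

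All of this ignores clustering by household and by PM+ group.

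**The case against.** Adjusting for the baseline value of the outcome is a standard choice, and pairing a lean primary model with a wider supporting one is legitimate. Nothing in the protocol is contradicted and no bias follows. All of that stands.

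Baseline HSCL-25 probably carries most of the prognostic information already. K10 measures much the same thing, and the eligibility cut-offs truncate both screening scores, so their added value may be close to nil. That stands too, and is why the range in the working starts near zero.

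A reader might infer that the stated 90% power would rise by one or two points. It would not: the 90% comes from an unadjusted comparison, while the covariates would act on variance left after baseline HSCL-25, where power is already about 96.5% at r = 0.5. A reader might also infer that the primary model rests on a single baseline reading. In fact it estimates differences at each visit, so HSCL-25 scores observed at other visits, including post-assessment, also inform it under dropout. Nor does the protocol say that K10 or WHODAS predicts attrition; that link is plausible but assumed.

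Gender is already named in the adjusted model, and the Randomization section describes no stratification by gender, so no design factor is left out of the primary model. The adjusted list is open-ended, so K10 and WHODAS may be intended there. The primary model, by contrast, is stated with one covariate.

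What survives is that complete, pre-randomisation, plausibly prognostic variables are not used in the decisive model, and using them costs almost nothing.

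**Conclusion.** The point holds as an optional gain in efficiency and robustness. The primary model is valid as written and the sample size stands. For an assumed joint partial R² of 0.01 to 0.10, the SE falls by about 0.5% to 5%. At d = 0.4 and r = 0.5 that is 0.1 to 1.3 points of power. It matters somewhat more if the true effect is smaller: 0.4 to 3.9 points at d = 0.3. These sizes rest on assumed correlations, 133 analysed per arm and no clustering. The missing-data benefit applies only if the added variables predict both dropout and outcome.

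The stronger reading, that the plan gives away a meaningful amount of precision or leaves the trial short of power, is not supported. The protocol contains no correlation that would show it, and zero gain lies within reasonable assumptions.

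**What to change.** In Statistical methods, before unblinding, list the primary model's covariates as baseline HSCL-25, screening K10, screening WHODAS and gender. Keep the wider model (age, education, traumatic experiences, post-migration difficulties) as the supporting analysis, and replace its open ending with a closed list.

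The cost is a one-line change and about three degrees of freedom on some 266 analysed participants. No new data are needed and no participant is lost. If the team prefers the single-covariate primary model, it remains acceptable.

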### Economic analyses

The economic analysis will be conducted from both a health sytem perspective, and from a broader perspctive including productivity impacts in order to determine the difference in costs and outcomes in Group PM+/E-CAU, compared with E-CAU. Costs will be compared between arms using a regression model, controlling for baseline, and with bootstrapped confidence intervals using 10,000 resamples. Incremental cost-effectiveness ratios (ICERs) will be calculated comparing changes in mean costs and primary outcomes from both payer and societal perspectives between the two groups. Non-parametric bootstrapping analyses, using 10,000 resamples, will be performed to account for uncertainty and derive 95% confidence intervals around ICERs in order to generate cost-effectiveness planes. Cost-effectiveness acceptability curves will be plotted to present the probability that the PM+/E-CAU intervention is cost-effective at various willingness-to-pay threshold levels.

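### The no-imputation rule rests on multilevel models, but it also covers cost and ICER analyses that are not described as multilevel

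*Protocol article*

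**What the plan says.** All of this is in the protocol article.

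- **Scope.** Statistical methods introduces what follows with "To estimate the effectiveness and cost-effectiveness of Group PM+, the following data analysis methods will be conducted".
- **Population.** The same section plans "Intention-to-treat (ITT) analyses, including all randomly assigned participants", with N given as 380.
- **Model.** "A linear mixed model will be used for the primary endpoint analysis to estimate the intervention effect", with participants as random effects. This model and its covariate-adjusted version are the only multilevel analyses described.
- **Missing data.** "Missing data will be treated as missing at random", followed directly by "No imputations of missing values will be made, as multilevel models can deal with missing data". No outcome or analysis is exempted.
- **Costs.** Economic analyses states: "Costs will be compared between arms using a regression model, controlling for baseline, and with bootstrapped confidence intervals using 10,000 resamples". It mentions no random effects, no repeated-measures structure and no handling of missing costs.
- **ICERs.** "Incremental cost-effectiveness ratios (ICERs) will be calculated comparing changes in mean costs and primary outcomes", with uncertainty from a non-parametric bootstrap.
- **Attrition.** Sample size and power calculations reads "Considering an expected 30% attrition at the 3-month follow-up". No figure is given for 12 months, the last assessment.

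**The concern.** A likelihood-based mixed model for repeated measures can do without imputation under missing at random, because a participant who misses one visit still contributes the visits attended. The reason given for the rule is therefore sound for the primary endpoint. A regression of cost on arm and baseline cost has no such mechanism: a participant whose cost is missing simply leaves the analysis. Bootstrapping does not help, since it describes sampling uncertainty and resamples whatever records are present.

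The rule thus removes imputation from analyses to which its justification does not apply. Followed as written, it sits badly with two other commitments in the same section: intention to treat on all 380, and an assumption of missing at random in its general form.

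The economic result carries weight. The Objectives section puts cost-effectiveness in the main objective, and the abstract's Discussion makes release of the manual and training materials wait until effectiveness and cost-effectiveness have been established. Any bias in the cost difference would pass into the ICER, the cost-effectiveness plane and the acceptability curve.

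**Working it through.** **1. Reproduce the plan's figures.** Inputs from Sample size and power calculations: d = 0.4, power 0.90, two-sided alpha 0.05, attrition 30%.

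- Normal approximation: n = 2(1.960 + 1.282)² / 0.4² = 131.4, so 132 per group. The t-test version gives 132.3, so 133, as stated.
- Attrition: 133 / 0.70 = 190 per group, 380 in total, as stated.

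**2. Participants left without imputation.** Records available = 380 × (1 − attrition).

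- At 30%: 380 × 0.70 = 266, so 114 participants are lost from any cost that needs the 3-month visit. This is an upper limit, because a participant may attend and still have incomplete cost data.
- The 12-month rate is not given. Over an assumed range, 35% leaves 247, 40% leaves 228 and 50% leaves 190.

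**3. What the precision figure means.** The standard error relative to full data on 380, with loss completely at random, is √(1/(1 − attrition)): 1.20 at 30%, 1.24 at 35%, 1.29 at 40% and 1.41 at 50%. This is the price of attrition, not of the no-imputation rule. Imputation recovers only the part carried by correlated observed data.

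**4. When is the complete-case cost regression valid?** It is unbiased when missingness depends only on arm and the baseline variables in the model. Missing at random also allows dependence on observed post-baseline data, such as an HSCL-25 score at post-assessment. That is where the two conditions part.

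**5. Illustration with assumed parameters (none from the protocol).**

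- Baseline b is standard normal.
- Interim score = 0.5b − 0.4·arm + 0.87·noise, observed for everyone.
- Cost = 0.3b + 0.4·interim + 0.8·noise. The true arm difference in cost is 0.4 × (−0.4) = −0.16, in units where the within-arm SD is about 1.
- 30% of costs are missing overall, with the log-odds of missingness linear in the interim score. The slope has either the same sign in both arms or opposite signs.
- 400,000 simulated participants for each slope.

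The last column predicts cost from arm, baseline and the interim score for everyone, as a stand-in for imputation.

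| Dropout pattern | Slope | Complete cases, baseline-adjusted | Using interim score |
|---|---|---|---|
| Same in both arms | 0.5 | −0.157 | −0.162 |
| Same in both arms | 1 | −0.149 | −0.166 |
| Opposite by arm | 0.5 | −0.249 | −0.162 |
| Opposite by arm | 1 | −0.327 | −0.169 |

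With slope 0, every estimate lies between −0.160 and −0.163. Complete-case bias is small when dropout works alike in both arms and large when it runs in opposite directions. Using the interim score brings the estimate back close to −0.16 in every case.

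**The case against.** The strongest reply concerns scope. The no-imputation sentence closes a paragraph about the mixed model, its reason names multilevel models, and Economic analyses is a separate section that does not mention imputation. Read that way, the rule never touches costs. All that remains is an unstated missing-data method for costs, which an article may leave to a fuller document. This reading is possible, but it is not what the sentence says: the rule has no restriction, and the section's opening covers cost-effectiveness. A fuller plan that imputed costs would have to contradict it.

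Other parts of the reply stand, and they rule out stronger claims that a reader might infer:

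- **That the protocol prescribes complete cases.** It does not say so. This is the default result of the rule applied to the named methods. The unspecified regression could be a repeated-measures cost model, though none is stated.
- **That missing any one visit loses a participant's whole cost.** The text gives no summation rule, recall period or costing horizon, and the figure showing the measures is not available here. A cost taken at one visit fits the text as well.
- **That complete cases need data missing completely at random.** They do not; see step 4. Nothing in the document suggests dropout running in opposite directions by arm.
- **That the rule itself inflates the standard error by 20% or more.** That figure measures attrition.
- **That costs and effects will rest on different participants.** This follows only if the ICER takes its effect from the mixed model and its cost from complete cases. Bootstrapping cost-effect pairs would avoid it, and the text does not say which is meant.

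**Conclusion.** The point holds in limited form. The plan states a blanket rule whose only justification does not extend to the cost regression and bootstrapped ICERs. Followed as written, those analyses would by default use only participants with observed costs, at most 266 of 380 where the 3-month visit is needed, at the plan's own attrition. They could then be biased under a form of missingness that the plan itself accepts.

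The size and direction of bias in this trial are unknown. The simulation shows only that it can range from negligible to material, depending on how dropout differs between arms. The conclusion assumes that the cost model is the single-level regression its description suggests, and that the rule applies as broadly as it is worded. It does not reach the primary mixed-model analysis or the sample size, which reproduces.

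**What to change.** - Limit the no-imputation sentence to outcomes analysed by mixed model.
- Under Economic analyses, name a method for costs and cost-effect pairs that is valid under the stated missing-at-random assumption. One option is multiple imputation carried out by arm, including baseline covariates and the observed interim CSRI and HSCL-25 data, combined with the planned bootstrap.
- State that incremental cost and incremental effect are estimated on the same randomised participants.
- Report the complete-case result as a sensitivity analysis.

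The cost is a change of wording and modest extra analysis work. No new data are needed. Trial status describes recruitment as still under way, so as of the article the change could be made before analysis.

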#### Other measures

A self-constructed questionnaire will be used to assess lifetime trauma exposure. This questionnaire includes items from the Harvard Trauma Questionnaire (HTQ) and the Post-traumatic Diagnostic Scale (PDS) and asks questions on specific traumatic experiences of Syrian refugees. It has 28 items scored as 0 (no) or 1 (yes), and the total score ranges from 0 to 28 [34, 35].

The Post-Migration Living Difficulties Checklist (PMLDC) will be used to assess post-migration stressors. The PMLDC has 17 items scored on a 5-point scale, ranging from 0 to 4 (0 = not a problem and 4 = very serious problem) (range 0–68). Items scored at least 2 (a moderately serious problem) are considered positive responses [36, 37].

If the validated Arabic version of the included measures is available, they will be selected and tested through cognitive interviews with Arabic-speaking adult Syrians. If the validated Arabic version of the measures is not available, these measures will be translated and back-translated in accordance with the WHO guidelines [38].

All randomly assigned participants, including those who discontinue, will be invited to all outcome assessments. In case participants do not attend a scheduled outcome assessment, they will be called a maximum of five times (on different days) to schedule a new appointment.

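### The reason given for banning all imputation covers missed follow-up outcomes only; a mixed model still drops participants whose baseline covariate is missing

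*Protocol article*

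**What the plan says.** All of the analysis text is in the protocol article under Statistical methods.

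- Analysis set: "Intention-to-treat (ITT) analyses, including all randomly assigned participants", with N given as 380. The ITT analyses are primary.
- Primary model: a linear mixed model with intervention as fixed effect, "baseline measurement of primary endpoint as covariate, and participants as random effects". The baseline HSCL-25 is thus a predictor and not one of the repeated responses.
- Covariate-adjusted model: formed by "adding pre-specified covariates at baseline (gender, age, education, traumatic experiences, post-migration difficulties, etc.) into the above model".
- Missing data: "Missing data will be treated as missing at random", followed by "No imputations of missing values will be made, as multilevel models can deal with missing data". The ban is not limited by variable or by visit.

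Two of the added covariates are multi-item scores, described under Other measures. Of the trauma questionnaire it says "It has 28 items scored as 0 (no) or 1 (yes), and the total score ranges from 0 to 28". Of the post-migration checklist it says "The PMLDC has 17 items scored on a 5-point scale", with a range of 0 to 68.

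**The concern.** The rule is wider than the reason given for it. Maximum likelihood for a mixed model uses whatever outcome visits a participant has, and under missing at random this needs no imputation of the missed visits. That property belongs to the response side of the model. The fixed-effect covariates are conditioned on and are given no distribution, so a participant with a blank covariate has no defined likelihood contribution. Standard software then removes all of that participant's records, including observed follow-up outcomes.

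Two things are at stake. First, follow-up data already collected would be discarded from a randomised comparison meant to include everyone. Second, the primary and adjusted models could rest on different people. A difference between their estimates could then come from the covariates or from the change of sample, and the adjusted model would be a weaker check on the primary result. Because the rule is stated outright, a later analysis plan that fills a covariate would contradict the published text.

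**Working it through.** **Step 1: the plan's own figure.** Inputs from Sample size and power calculations: d = 0.4, two-sided α = 0.05, power 0.90, 30% attrition at 3 months.

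- Normal approximation: n = 2(1.960 + 1.282)²/0.4² = 131.4, rounded up to 132 per arm. The t-based solution is 132.3, rounded up to 133, the stated minimum.
- Attrition: 133/0.70 = 190 per arm, 380 in total, as stated.
- Margin: 190 × 0.70 = 133. The attrition allowance uses up the whole margin, so nothing is set aside for participants lost through a covariate.

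**Step 2: which gaps the mixed model covers.**

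| What is missing | Role | Covered by the likelihood under missing at random? | Model affected |
|---|---|---|---|
| HSCL-25 at a follow-up visit | Response | Yes, the other follow-up visits are used | None |
| HSCL-25 at baseline | Fixed covariate | No, participant omitted | Primary and adjusted |
| Gender, age, education | Fixed covariate | No, participant omitted | Adjusted only |
| Trauma score (28 items) | Fixed covariate | No, participant omitted | Adjusted only |
| Post-migration score (17 items) | Fixed covariate | No, participant omitted | Adjusted only |

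Only the first row matches the reason given for the ban. The primary model is exposed through one covariate. The adjusted model is exposed through that one, five more, and whatever the list's open ending adds.

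**Step 3: size, as an illustration.** The article gives no rate, so let c be the assumed share of participants lacking at least one covariate that a model needs. Assume they are spread evenly over arms and over those with and without 3-month data. Participants lost = 380c; effective n per arm at 3 months = 133(1 − c); power ≈ Φ(0.4 × √(n/2) − 1.96).

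| c | Lost of 380 | n per arm | Approximate power |
|---|---|---|---|
| 0 | 0 | 133 | 0.904 |
| 1% | 3.8 | 131.7 | 0.901 |
| 5% | 19 | 126.4 | 0.889 |
| 10% | 38 | 119.7 | 0.872 |

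This is a plain two-group comparison at 3 months. It ignores other visits and the gain from baseline adjustment, so it shows only the order of the loss: at most 0.904 − 0.872 ≈ 0.03 over this range. Power is the lesser issue; the change of analysis population is the greater one.

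**The case against.** The strongest defence is context. The ban comes straight after the mixed model and the missing-at-random statement, and its reason concerns multilevel models, so its authors may have had only missed follow-up visits in mind. That is a fair guess at intent, but the sentence speaks of missing values without limit. If the narrow scope is intended, saying so costs nothing.

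A second defence is that the exposure is small. Baseline comes before randomisation (Participant exclusion criteria; Randomization), and the larger set of covariates enters only an additional model. This stands, and it keeps the point modest for the primary analysis. It does not remove it, since the article does not make complete covariates a condition of randomisation.

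A third defence is that a mean-filled trauma score may understate the trauma of someone who declined to answer. That is true of the individual value and of the covariate's coefficient. The treatment contrast is another matter: the filled value depends on neither arm nor outcome, so it does not bias that contrast.

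A reader might go further and infer that one blank item voids a whole HSCL-25 score, so that primary data and power are lost item by item. The documents do not support this. They nowhere say that a single missing item voids a score, and they do not say whether the HSCL-25 is a sum or an item mean; a mean over answered items needs no separate imputation step. Item-level scoring is commonly left to a scoring manual or analysis plan, neither of which is shown. A reader might also infer that the people dropped would be those with the worst histories. That is possible for sensitive questions, but nothing in the article establishes it.

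**Conclusion.** The concern holds for baseline covariates. The stated reason justifies not imputing missed follow-up outcomes; it does not justify leaving covariates blank. Applied as written, the rule removes from the primary model anyone without a baseline HSCL-25 score, and from the adjusted model anyone lacking any listed covariate, despite the ITT set of all 380.

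The size cannot be derived from the article. It is probably small for the primary model and larger, possibly selective, for the adjusted one. The conclusion rests on two things: the ban is read as unrestricted, as it is worded, and the covariates enter as fixed effects, as the article states. It rests on no assumption about how partly answered scales are scored.

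**What to change.** Change the missing-data text in two places.

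1. Limit the no-imputation rule to missed outcome assessments, where likelihood estimation under missing at random is the reason.
2. Add that any missing baseline covariate, including the baseline HSCL-25, is filled with the mean of both arms combined, computed blind to arm. For gender and education this means the pooled mean of each indicator variable.

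Every participant with at least one follow-up outcome then stays in both models, so the two estimates refer to the same people. Participants with no follow-up at all still contribute nothing to these models; the change does not claim otherwise. The method is suitable because the covariates are measured before randomisation and serve only for adjustment.

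The cost is two sentences and a few lines of code, with no new data. The downside is slightly less precise covariate adjustment for the participants filled in. A proration rule for partly answered scales can be left to the scoring manual or the analysis plan.
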